### Treatments

#### *Treatment as usual (TAU)*

This is pharmacological and supportive psychosocial treatment according to the needs and current regime of the patient. The amount of contact with health care professionals outside of our department will be registered. In addition, patients will be offered biweekly consultations with either a psychologist or a medical doctor from our study.

#### *Cognitive behavioral therapy for insomnia (CBT-I)*[14]

This is a multicomponent treatment usually consisting of one or more of the following interventions: sleep restriction therapy, psychoeducation about sleep, stimulus control, and challenging beliefs and perception of sleep. Bipolar patients may be prone to misperceive sleep for wakefulness
[3,32]. There will also be a focus on challenging and correcting sleep state misperception using cognitive and behavioral techniques
[33]. Circadian rhythm is likely to be disturbed in the included patients, so there will be particular emphasis on stabilization of the circadian rhythm. Chronotherapeutic interventions of light therapy and gradual sleep phase advancement are currently the best available treatment options for circadian rhythm disturbances
[34]. If necessary, these interventions will be included, to stabilize the circadian rhythm. The treatment will last for three to eight sessions. The therapists will be two clinical psychologists and one psychiatrist. Therapists will have received training in CBT-I and have one to nine years of clinical experience with CBT-I. Patients will be given checks for treatment credibility. Therapy sessions will be checked for adherence to manual by having at least two therapists present during treatment.

### Withdrawal criteria

Patients will be withdrawn from the study if the clinician finds that the patient is in need of, or better served with, other treatment; if exclusion criteria are met; if the clinical condition gets significantly worse according to the clinicians’ judgment; or if patients withdraw their consent. All patients prematurely discontinuing the trial will be seen for a final evaluation. The date and reason for discontinuation will be noted.

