## Methods

### Study design

The study is a randomized controlled trial aimed to study the efficacy of CBT-I in euthymic bipolar disorder patients with comorbid insomnia compared with TAU. Patients will be recruited from the Department of Psychiatry, St. Olav’s University Hospital, Trondheim, Norway. They must fulfill criteria for SCID-1 (Structured Clinical Interview for DSM Disorders) verified bipolar I or II disorder and be euthymic, as defined by a score on the Montgomery Åsberg Depression Rating Scale (MADRS) not higher than 13 or by a score on the Young Mania Rating Scale (YMRS) not higher than seven. In addition, patients must fulfill the DSM-IV diagnosis criteria of ‘insomnia related to another mental disorder’ as assessed by the Insomnia Interview Schedule (IIS)
[14]. Patients will not be accepted if they meet any of the following exclusion criteria: they are in an affective episode; they work night shifts; they have an ongoing alcohol or substance abuse problem, or sleep apnea or other confounding sleep disorders, or medical conditions that may account for a sleep disturbance; or they have conditions or cognitive impairments incompatible with participation. Patients must not have been in a defined episode in the previous month or have been hospitalized in the previous two months. Any prophylactic medication of the participants must be accepted by a doctor in the study.

Patients meeting criteria for inclusion will enter a run-in phase consisting of three weeks, during which they will complete a sleep and mood diary and a register of adherence to medication. In the last of these three weeks, they will be monitored for seven consecutive days with an actigraph and for two nights using ambulatory polysomnography. The patients will be assigned a patient number and sign a consent form after receiving oral and written information about the study prior to undergoing study procedures. The patients will receive US $85 in compensation for each polysomnography session, and another US $85 in compensation for transport costs and other expenses related to participation. Those patients who are able to complete the three-week run-in phase and meet diagnostic criteria for insomnia will then be randomized to the treatment trial. Figure 
1 summarizes the study design and Table 

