### Sample size calculation

#### A-priori power calculations

The primary response variable, change in ISI score between baseline and endpoint, will be analyzed with the independent samples *t* test at a significance level of *α* = 0.05. Prior studies of CBT-I for patients with mental disorders and comorbid insomnia have found between-group effect sizes in a range from *d =*1.1 to *d =* 1.6 on the ISI. Thirty-six patients are required to have a 90% chance of detecting a between-group effect size of *d* = 1.1 at a significance level of *α =* 0.05*.* This corresponds to a change in ISI score from 18 in the control group to 14 in the CBT-I group given a standard deviation of 3.6.

In addition, secondary response variables of total sleep time, sleep efficiency, and changes in polysomnography parameters will be recorded. Daily and weekly variations in mood and time to relapse to a new episode will also be compared between the two groups.

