## Discussion

This study will test whether treatment with CBT-I can provide improvement in sleep quality and will also be one of the first to test the effects of CBT-I on patients with insomnia and bipolar disorder. Insomnia is associated with several negative health outcomes in the general population
[7]. It is likely that patients with bipolar disorder and insomnia, in addition to the same negative consequences, have an increased risk of experiencing new episodes of depression or (hypo) mania.

We are not aware of side effects related to CBT-I, but as it is an untested treatment in bipolar disorder, we do not know if it may trigger new episodes of depression or mania
[35]. The extensive study program may become a potential problem for inclusion of participants and completion of study procedures. Motivational work will be all-important before and during treatment in both groups.

Descriptions of quality of sleep in euthymic periods of bipolar disorder are important for planning interventions and improving monitoring for signs of recurrence of new episodes of depression or (hypo) mania.

It is important to compare the value of diagnostic tools, such as sleep diaries, actigraphs and polysomnography, in order to improve the quality of diagnosis and possibly to simplify the clinical practice of such tools
[36].

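### Patients who worsen, need other treatment or meet an exclusion criterion leave the study and not only the treatment, so scheduled ISI, sleep, mood and relapse follow-up is lost in an outcome-dependent way

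*Protocol article*

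**What the plan says.** Under Withdrawal criteria, the Protocol article states: "Patients will be withdrawn from the study if the clinician finds that the patient is in need of, or better served with, other treatment". The further grounds are "if exclusion criteria are met; if the clinical condition gets significantly worse", the latter as judged by the clinicians, and withdrawn consent. The same section adds two safeguards: "All patients prematurely discontinuing the trial will be seen for a final evaluation" and "The date and reason for discontinuation will be noted".

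Study design lists among the exclusion criteria that "they are in an affective episode". A-priori power calculations states: "Daily and weekly variations in mood and time to relapse to a new episode will also be compared between the two groups". The Discussion says of CBT-I in bipolar disorder that "we do not know if it may trigger new episodes of depression or mania".

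The ISI, the primary outcome, is scheduled before treatment, after treatment and at six months (Insomnia Severity Index; Table 1). Statistics limits the efficacy analyses to patients with post-baseline efficacy measurements, and plans both a completer analysis and linear mixed models.

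**The concern.** The rule treats two decisions as one: whether a patient continues the study treatment, and whether the patient continues to be measured. Three of its four grounds depend, or can depend, on how the patient is doing. Scheduled data would then be missing because of the outcome.

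The loss may also differ between arms. Worsening and need of other treatment are judged by clinicians with no stated threshold. The only person described as blinded is the doctor who reads the polysomnographs, and those who deliver CBT-I necessarily know the allocation. Contact differs too: three to eight therapy sessions in one arm, and the offer of biweekly consultations in both or in TAU only, depending on how the Treatments section is read.

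At stake are the between-group comparison on the ISI, the relapse comparison, and the article's own open question of whether CBT-I may provoke episodes. An analysis plan cannot recover measurements that were never taken.

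**Working it through.** **1. The passages side by side**

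- Withdrawal is from the study, and meeting an exclusion criterion is one ground.
- Being in an affective episode is an exclusion criterion.
- Hence a new episode after randomization can end participation, while time to a new episode is compared between groups.
- A patient withdrawn before week 8 has no scheduled post-baseline ISI. One withdrawn later has no 6-month ISI, diary, actigraphy or polysomnography.
- A patient with no post-baseline measurement then falls outside the efficacy set. The mixed model does not repair this: it assumes data missing at random and gains little from a patient with a baseline value only.

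**2. The plan's own figure**

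Inputs from A-priori power calculations: d = 1.1, α = 0.05 (two-sided assumed), power 90%, ISI 18 versus 14, SD 3.6.

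n per arm = 2(1.960 + 1.282)² / 1.1² = 17.4, rounded up to 18, so N = 36. This reproduces the stated 36. By the t test, power at 18 per arm is 89.4%. The total contains no allowance for withdrawal.

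**3. Size of a selective loss**

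The documents give no withdrawal rate, so everything here is an assumption. Take 18 per arm, SD 3.6 and no true effect. Remove m patients from one arm only, ranked by a withdrawal tendency that correlates ρ with the ISI result. The expected spurious difference is

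bias = ρ × 3.6 × S_m / (18 − m),

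where S_m is the expected sum of the m largest of 18 standard normal values (by simulation S_2 = 3.17, S_3 = 4.24, S_4 = 5.09). At ρ = 1:

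- m = 2: 3.6 × 3.17 / 16 = 0.71
- m = 3: 3.6 × 4.24 / 15 = 1.02
- m = 4: 3.6 × 5.09 / 14 = 1.31

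Halving these gives ρ = 0.5. Type I error of the t test comes from simulation (20,000 to 40,000 replicates):

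| Lost from one arm | Bias, ρ = 0.5 | Type I error, ρ = 0.5 | Bias, ρ = 1 (exactly the worst) | Type I error, ρ = 1 |
|---|---|---|---|---|
| 2 of 18 | 0.36 | about 6% | 0.71 | about 10% |
| 3 of 18 | 0.51 | about 7% | 1.02 | about 15% |
| 4 of 18 | 0.65 | about 8% | 1.31 | about 20% |

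Against the planned 4 points, the ρ = 0.5 column is 9 to 16% of the effect and the ρ = 1 column 18 to 33%. At ρ = 0.3 the type I error is about 6%. If both arms lose patients in the same way, the mean bias is about zero. If TAU loses more, the sign reverses and CBT-I looks worse than it is.

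**4. Loss of power**

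Losing 20% of each arm at random leaves 14.4 per arm and a t-test power of 81.2%. Any dropout would have this effect. It is not specific to the withdrawal rule.

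**The case against.** A reader might infer that patients who relapse or are harmed vanish from the data, and that time to relapse is censored at or just before the event. The documents do not support that. Every patient who discontinues is seen for a final evaluation, the date and reason are noted, and medication changes, hospitalizations and other changes in care are registered with dates. No censoring rule is stated. A relapse that triggers withdrawal can therefore be counted on its date, and harm can be read from the reasons. What stands is narrower: patients withdrawn for worsening or for other treatment, short of a defined episode, are informatively censored for relapse.

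It is also fair to say that the instruments of the final evaluation may be listed in a full protocol that is not shown, and an ISI may be among them. A mixed model could use such a value. It would still not be the 8-week or 6-month ISI.

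The link from relapse to withdrawal is the natural reading but not the only one. The exclusion criteria are worded as entry conditions, and the withdrawal ground may be meant for criteria discovered during run-in, such as sleep apnea. Worsening and need of other treatment lead to the same loss without that link.

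Finally, the upper figures in the table are an extreme. They put all losses in one arm and make those lost exactly the worst on the ISI, whereas the rule acts on clinical condition and not on ISI rank. Patients are also euthymic at entry, with no episode in the previous month, and treatment lasts eight weeks. Exposure is therefore probably smaller for the 8-week ISI than for the six-month follow-up. All of this limits the size but does not remove the mechanism.

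**Conclusion.** The point holds in a limited form. As written, the rule ends scheduled follow-up for reasons tied to the outcome, under clinicians who know the allocation, and the efficacy set then leaves out those without post-baseline data. The relapse event itself need not be lost.

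Neither the rate nor the direction of the bias can be derived from the documents. Under the assumed one-sided loss of 2 to 4 patients, a plausible size is about 0.4 to 0.6 ISI points with a type I error of 6 to 8%. The ceiling is 0.7 to 1.3 points with 10 to 20%. A reader might infer that the trial is biased in favour of CBT-I. That does not follow, since heavier withdrawal in TAU would bias it the other way. The reason to act is that the missing data cannot be recovered later, in a trial of 36 patients where each loss weighs.

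**What to change.** - State separately the stopping of study treatment and the leaving of the study. Unless consent is withdrawn, collect at least the web-based ISI, BDI and Altman scale and the dated registrations at 8 weeks and 6 months for every randomized patient.
- Count withdrawal because of an affective episode as a relapse event on its recorded date.
- Reconcile Study design, Withdrawal criteria and A-priori power calculations on what a new episode after randomization means for study participation. The clinical decisions, including when treatment is stopped or changed, remain with the clinicians.

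The cost is a change of wording and reminders to a few patients for questionnaires that are already set up. Some of the later data will reflect other treatment, which the report should say.

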### Sample size calculation

#### A-priori power calculations

The primary response variable, change in ISI score between baseline and endpoint, will be analyzed with the independent samples *t* test at a significance level of *α* = 0.05. Prior studies of CBT-I for patients with mental disorders and comorbid insomnia have found between-group effect sizes in a range from *d =*1.1 to *d =* 1.6 on the ISI. Thirty-six patients are required to have a 90% chance of detecting a between-group effect size of *d* = 1.1 at a significance level of *α =* 0.05*.* This corresponds to a change in ISI score from 18 in the control group to 14 in the CBT-I group given a standard deviation of 3.6.

In addition, secondary response variables of total sleep time, sleep efficiency, and changes in polysomnography parameters will be recorded. Daily and weekly variations in mood and time to relapse to a new episode will also be compared between the two groups.

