### Data collection and randomization

Clinical interviews and registrations will be conducted by a psychiatrist, medical doctor, or clinical psychologist at the Bipolar Clinic, Østmarka Department of Psychiatry, St. Olav’s University Hospital, Trondheim, Norway. The insomnia diagnosis will be assessed before randomization, and at a six-month follow-up. The polysomnographs will be administered by the Department of Clinical Neurophysiology at St. Olav’s University Hospital and assessed by a blinded medical doctor. The actigraphy recordings will be administered by the clinician in charge of treatment of each patient. Except for the daily assessments of mood and sleep, the patient-reported measures will be collected using a secure internet-based interface, but patients will be given the option of completing the paper-version of the self-reported measures at the clinic instead.

Patients will be randomized to CBT-I or TAU by a web-based system developed and administered by the Unit of Applied Clinical Research, Norwegian University of Science and Technology (NTNU), Trondheim, Norway. Eligible patients who have signed the consent form and fulfill criteria for participation will be randomized sequentially, in blocks of variable size to ensure an even allocation throughout the study.

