### Statistics

Categorical variables will be analyzed using chi-square tests. Ordinal variables will be analyzed using nonparametric tests in addition to using Student’s *t* tests, analysis of variance (ANOVA) and analysis of covariance (ANCOVA) with baseline values as covariates. The time to change in treatment for bipolar disorder will be analyzed using survival analysis. Linear mixed models will be applied in analyses of treatment response. All patients who fulfill baseline registration will be included in the analysis of baseline characteristics. All subjects who receive at least one session of CBT-I and provide post-baseline efficacy measurements will be included in efficacy data analyses. Analyses including only patients fulfilling the treatment will also be conducted.

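### The primary ISI analysis is a valid and correctly sized t test on change, but ANCOVA with baseline ISI would be more precise at almost no cost

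*Protocol article*

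**What the plan says.** All references are to the Methods of the protocol article.

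- **A-priori power calculations** ties one test to the primary outcome: "The primary response variable, change in ISI score between baseline and endpoint, will be analyzed with the independent samples". The test meant is Student's t, with alpha set to 0.05. No covariate is mentioned.
- The same section gives the sample size for *d* = 1.1: "Thirty-six patients are required to have a 90% chance of detecting a between-group effect size of" that value. It translates this into ISI points: "This corresponds to a change in ISI score from 18 in the control group to 14 in the CBT-I group". The SD behind this step is 3.6, and the section does not say whether that is the SD of the change or of the score at one visit.
- **Data collection and randomization** describes randomization "in blocks of variable size to ensure an even allocation throughout the study", which gives 18 per arm.
- **Table 1** and the **Insomnia Severity Index** paragraph have ISI measured before treatment, after treatment and at six months, so every analysed patient should have a baseline value.
- **Statistics** lists, for ordinal variables, nonparametric tests, t tests, "analysis of variance (ANOVA) and analysis of covariance (ANCOVA) with baseline values as covariates". It then adds: "Linear mixed models will be applied in analyses of treatment response". It does not say whether ISI is among the ordinal variables, or how any of these analyses relates to the primary t test.

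**The concern.** The only test that the plan attaches by name to its primary outcome uses baseline ISI by subtraction alone. Subtraction assumes that a patient who starts one point higher will also finish one point higher. When the correlation between the two measurements is below 1 and the SDs are similar, that over-corrects, and noise in the baseline measurement is carried into the outcome. ANCOVA estimates the slope from the data instead.

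At 18 patients per arm, a chance difference in mean baseline ISI is quite possible. The change score over-corrects for such a difference, whereas ANCOVA adjusts for it by the estimated slope. What is at stake is the precision of the primary estimate, and some power, in a small trial that already collects the data needed to do better. The plan also names the better method but leaves its link to the primary outcome unstated.

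**Working it through.** **Inputs.** From the power section: two-sample t test, alpha 0.05, power 90%, *d* = 1.1, means 18 and 14, SD 3.6, total 36. From the randomization section: even allocation, so n = 18 per arm. Two assumptions are needed. Alpha is taken as two-sided, because a one-sided test would need only 28 to 30 patients and does not reproduce 36. The baseline-to-endpoint correlation r is not in the document and is varied from 0.3 to 0.7.

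**Step 1: reproduce the plan's figure.** By the normal approximation, n per arm = 2(1.960 + 1.282)²/1.1² = 2 × 10.507/1.21 = 17.4, rounded up to 18, so 36 in total. This matches. The translation into points is consistent too: (18 − 14)/3.6 = 1.11. With the noncentral t distribution (34 df), power at 18 per arm is 89.4% for *d* = 1.1 and 89.9% for *d* = 4/3.6. Strictly, that method gives 19 per arm for 90%, a difference of two patients that is of no consequence.

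**Step 2: compare the variances.** Let σ₀ and σ₁ be the SDs of ISI at baseline and endpoint.

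- Change score: σ₁² + σ₀² − 2rσ₀σ₁
- ANCOVA residual: σ₁²(1 − r²)
- Difference: (σ₀ − rσ₁)², which is never negative

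Apart from the one degree of freedom, ANCOVA is therefore never less precise. With equal SDs σ, the two variances are 2σ²(1 − r) and σ²(1 − r²), and their ratio is (1 + r)/2: 0.65, 0.75 and 0.85 at r = 0.3, 0.5 and 0.7.

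**Step 3: power at 18 per arm for a 4-point difference.** The noncentrality is (4/SD) × √(18/2) = 12/SD, with 34 df for the t test and 33 df for ANCOVA.

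*Reading A: 3.6 is the SD of the change.* The t test has SD 3.6 whatever r is. The ANCOVA SD is 3.6√((1 + r)/2).

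| r (assumed) | SD, t test | Power, t test | SD, ANCOVA | Power, ANCOVA |
|---|---|---|---|---|
| 0.3 | 3.60 | 89.9% | 2.90 | 98.0% |
| 0.5 | 3.60 | 89.9% | 3.12 | 96.2% |
| 0.7 | 3.60 | 89.9% | 3.32 | 93.9% |

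*Reading B: 3.6 is the SD of the score at each visit.* The SD of the change is 3.6√(2(1 − r)). The ANCOVA SD is 3.6√(1 − r²).

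| r (assumed) | SD, t test | Power, t test | SD, ANCOVA | Power, ANCOVA |
|---|---|---|---|---|
| 0.3 | 4.26 | 78.1% | 3.43 | 92.4% |
| 0.5 | 3.60 | 89.9% | 3.12 | 96.2% |
| 0.7 | 2.79 | 98.7% | 2.57 | 99.5% |

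The two readings coincide at r = 0.5, where √(2(1 − r)) = 1.

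**Step 4: does the planned mixed model already recover the loss?** Not by itself. With complete data at two visits and an unconstrained group-by-time term, its treatment contrast is the difference in mean change, which is what the t test estimates. It gains the ANCOVA precision only if baseline ISI is a covariate or the baseline means are constrained to be equal across arms. The article specifies neither, and at this level of detail it need not.

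**The case against.** The strongest defence is that nothing here is invalid. In a randomized trial, a t test on change is unbiased and holds its type I error, and the article powers the test that it names. Covariates and model details are often left to an analysis plan, which may exist but is not shown. All of this stands, except that here the article does not leave the choice open: it states a primary test without a covariate. The point is therefore one of efficiency, not error.

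A reader might infer three stronger things that the document does not support.

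- **That the trial is underpowered.** A shortfall appears only if 3.6 is the SD of a single score and r is below 0.5. The values 18 and 14 do look like endpoint scores, which favours that reading. But the variable being sized is defined as a change, and if 3.6 is its SD, power is about 90% for every r.
- **That ANCOVA is reserved for other outcomes.** The Statistics section names it for ordinal variables and excludes none. ISI, a questionnaire score, could fall under that heading, so a baseline-adjusted ISI analysis may already be intended in some role.
- **That several tests and two follow-up visits leave the primary result open to selection, with an inflated type I error.** The power section binds the primary outcome to one test. A plan cannot be charged both with fixing a less efficient test and with leaving the test open. Any inflation figure would also depend on which tests one chose to put in the set. The word endpoint is not tied to a week, but the abstract describes an eight-week treatment trial and the measures sections call six months the follow-up, so end of treatment is the natural meaning. Naming the week is a clarification of wording.

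**Conclusion.** The point holds as a nearly free improvement. Under the assumptions of equal SDs at both times, a 4-point difference and r between 0.3 and 0.7, ANCOVA adds about 4 to 8 percentage points of power if 3.6 is the SD of the change. If 3.6 is the SD of a single score, it adds about 14 points at r = 0.3, 6 at r = 0.5 and 1 at r = 0.7. The direction of the gain does not depend on which SD is meant; its size does, and r is an assumption throughout. There is no error in the sample size and no threat to the validity of the planned test.

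**What to change.** In the power section and the Statistics section, name one primary analysis: ISI at the end of treatment (week 8), compared between arms by ANCOVA with baseline ISI as covariate. An equivalent choice is the week-8 contrast from a linear mixed model that adjusts for baseline ISI or constrains the baseline means to be equal.

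Make the t test on change, the nonparametric test and the six-month contrast secondary or sensitivity analyses, and say so where the Statistics section lists them. State whether 3.6 is the SD of the change or of a single ISI score and, if it is the latter, the correlation assumed.

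The cost is a few sentences and one degree of freedom (33 instead of 34). No new data are needed, and the sample size can stay at 36.

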[11]. Although evidence of the effectiveness of CBT-I has existed for more than 20 years, it has not been introduced to patients who also suffer from bipolar disorder
[12]. Between-group effect sizes for CBT-I are usually in the range of 1.0 to 1.6, as measured with the Insomnia Severity Index (ISI)
[12,13].

Although it is well documented that sleep is disturbed in bipolar disorder, there is less knowledge about how sleep is disturbed
[3]. There is evidence to suggest that sleep in bipolar disorder is characterized by circadian rhythm disturbance, as in patients with delayed sleep phase syndrome, as well as by maladaptive cognitive and behavioral strategies, as in otherwise healthy individuals with insomnia
[3]. Descriptive studies of frequency and type of sleep disturbance in euthymic patients with bipolar disorder are needed to improve treatment. Data from this trial will be used in a micro- and macroscopic description of the character of sleep disturbance in patients with euthymic bipolar disorder and comorbid sleep disturbance.

Sleep diaries, actigraphy, and, more seldom, polysomnography have traditionally been used to measure the effects of sleep interventions. Polysomnography is considered the best objective monitoring system and the only way to assess the constitution of sleep stages, including changes in slow wave sleep and rapid eye movement sleep, whereas subjective descriptions of sleep quality are better predictors of functional impairment and emotional distress
[11].

The aims of this randomized controlled trial are to compare CBT-I and treatment as usual (TAU) with treatment as usual alone in improving quality of sleep, stabilizing minor mood variations, and preventing new mood episodes in euthymic patients with bipolar disorder and comorbid insomnia. In addition, the study will compare the use of sleep diaries, actigraphy, and polysomnography, in order to possibly simplify registrations of sleep for clinical use.

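### The 90% power assumes complete outcome data on all 36 patients and an SD whose scale is not stated, so the plan's inputs do not fix the power of its change-score test

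*Protocol article*

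**What the plan says.** All references are to the protocol article.

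- **A-priori power calculations, test:** "The primary response variable, change in ISI score between baseline and endpoint, will be analyzed with the independent samples" *t* test, at α = 0.05. Sidedness is not given.
- **A-priori power calculations, size:** "Thirty-six patients are required to have a 90% chance of detecting a between-group effect size of" d = 1.1. The lower limit of a range from earlier CBT-I studies in patients with mental disorders and insomnia is the planning value. It is then illustrated as a "change in ISI score from 18 in the control group to 14 in the CBT-I group given a standard deviation of 3.6".
- **Data collection and randomization:** blocks of variable size, intended to keep the arms equal, so 18 per arm.
- **Statistics:** the efficacy analyses need post-baseline efficacy data. ANCOVA with baseline covariates and linear mixed models are listed among the methods.
- **Withdrawal criteria:** several routes out of the study, including clinician judgment and withdrawn consent. Patients who stop early get a final evaluation.
- **Discussion:** "The extensive study program may become a potential problem for inclusion of participants and completion of study procedures".
- **Trial status:** recruitment runs to a planned date or until the necessary number has been included. The number is not repeated there, and 36 is the only one the article gives.

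**The concern.** Two things are left open in a calculation that otherwise looks fully specified.

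First, 36 is the number that must be *analysed* to reach about 90%, but it reads as the number to be *included*. Nothing is held in reserve for the losses the article itself expects.

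Second, the tested variable is change in ISI, while 18 and 14 read as the two groups' score levels, not as changes. The article does not say whether 3.6 is the SD of scores or of change. The two agree only at one particular baseline-endpoint correlation, and no correlation is given.

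At stake is how a null result would be read. It would be set against 90% power, a figure that needs complete data on every patient and an unstated SD assumption.

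**Working it through.** **Inputs from the article:** d = 1.1; difference 18 − 14 = 4; SD 3.6, so 4/3.6 = 1.11; α = 0.05; 18 per arm.

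**Assumed, because not given:** two-sided test (one-sided would give 94.4%, so two-sided fits the stated 90%); loss rates; baseline-endpoint correlation r; equal SDs at both times.

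**1. Reproducing the stated figure.**

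- Normal approximation: n per arm = 2(1.960 + 1.282)²/1.1² = 17.4, rounded up to 18, so 36 in total. Power at 18 per arm is 91.0%.
- Exact noncentral t: df = 34, noncentrality = 1.1 × √(18/2) = 3.3. Power is 89.4% at d = 1.1 and 89.9% at d = 1.11. Strictly reaching 90% takes 19 per arm (91.0%).

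The stated 36 and 90% are reproduced, with no slack.

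**2. Loss from 36 (noncentral t, d = 1.1).**

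| Assumed loss | Evaluable | Power |
|---|---|---|
| 0% | 36 | 89.4% |
| 5% | 34.2 | 87.7% |
| 10% | 32.4 | 85.8% |
| 15% | 30.6 | 83.6% |
| 20% | 28.8 | 81.2% |

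Keeping 36 evaluable would take 36/(1 − loss) patients, rounded up: 40 at 10%, 43 at 15% and 45 at 20%.

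**3. Scale of the SD.** If 3.6 is the SD of ISI scores at both times, the SD of change is 3.6 × √(2(1 − r)). This equals 3.6 only at r = 0.5. For ANCOVA of endpoint ISI on baseline ISI, the residual SD is 3.6 × √(1 − r²). The difference is held at 4 points.

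| Assumed r | SD of change | t test on change, 36 | t test on change, 30 | ANCOVA SD | ANCOVA, 36 | ANCOVA, 30 |
|---|---|---|---|---|---|---|
| 0.3 | 4.26 | 78% | 70% | 3.43 | 92% | 87% |
| 0.4 | 3.94 | 84% | 76% | 3.30 | 94% | 89% |
| 0.5 | 3.60 | 90% | 84% | 3.12 | 96% | 92% |
| 0.6 | 3.22 | 95% | 91% | 2.88 | 98% | 96% |
| 0.7 | 2.79 | 99% | 97% | 2.57 | 99% | 98% |

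Spending one more degree of freedom on the covariate changes the ANCOVA figures by about 0.1 percentage point or less.

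The ratio of ANCOVA to change-score variance is (1 − r²)/(2(1 − r)) = (1 + r)/2. It is below 1 for any r below 1, so ANCOVA is the stronger test at every correlation shown.

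**The case against.** **The calculation is not wrong.** This is right. Both N and power reproduce, and 89.4% or 89.9% rounds to roughly 90%. The point concerns what the figure assumes.

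**The power rests on a standardised d from earlier studies, and the 18/14/3.6 line only illustrates it.** This is also fair. A score-scale SD matters only if the 4-point difference is held fixed, and it moves power in either direction: above r = 0.5 the change-score test exceeds 90% and could absorb some loss. With 30 evaluable it still has 91% at r = 0.6. What stands is that the illustration does not match the tested variable and leaves the SD's scale open.

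**A condensed article may leave inflation to the full protocol, and that 36 is the inclusion target is an inference.** Both are true. In addition, only patients who complete the run-in are randomized, ISI is a short self-report that can be completed online or on paper, early leavers are seen once more, and mixed models can use partial data. These may keep the loss small. However, the article does not say that ISI is collected at the final evaluation. It also states N, α, power, d, means and SD in full, and links recruitment to a necessary number without saying whether that number means included or evaluable patients.

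**Stronger readings that a reader might infer.** One is that the design does not deliver 90%. The article gives neither a loss rate nor a correlation, so this cannot be shown. Another is that the Background, where effects are "Between-group effect sizes for CBT-I are usually in the range of 1.0 to 1.6, as measured with the Insomnia Severity Index (ISI"), contradicts the 1.1 used for planning. It does not: the Background sentence describes CBT-I effects generally, while the power section cites studies in patients with mental disorders and comorbid insomnia.

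**Conclusion.** The concern holds as a matter of unstated assumptions. The 90% applies to 36 patients with outcome data (exact 89.4% at d = 1.1) and carries no visible allowance for the loss that the article foresees. If 36 is the inclusion target, as it appears to be, an assumed 15-20% loss leaves about 84-81% at that d.

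The SD's scale is a second, independent uncertainty. Read as a score SD, with the 4-point difference kept and 36 evaluable, 3.6 gives change-score power from 78% (r = 0.3) through 90% (r = 0.5) to 99% (r = 0.7). True power may therefore be below or above 90%, and the article does not let a reader tell which. The loss rates, the correlations and equal SDs over time are assumptions of this check, not figures from the article.

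**What to change.** 1. Restate the power for evaluable patients, for example: *36 evaluable patients give about 89% power at d = 1.1 (two-sided α = 0.05); with an assumed 15-20% loss, about 84-81%.* Say whether 36 counts patients included, randomized or evaluable.
2. State whether 3.6 is the SD of ISI scores or of change, and give the baseline-endpoint correlation assumed. Present 18 and 14 as score levels if that is what they are.
3. Make ANCOVA of endpoint ISI with baseline ISI as covariate the primary test in place of the change-score t test. The Statistics section already lists the method. With a score SD of 3.6 and assumed r = 0.3-0.5, power is 92-96% with 36 evaluable and 87-92% with 30.

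**Cost:** items 1 and 2 are wording, at the price of a less favourable stated figure for the t test. Item 3 uses data already being collected and needs no more patients. It offsets much of the likely loss but does not guarantee 90%: with 30 evaluable it falls short at r = 0.3 (87%) and r = 0.4 (89%). If 90% must be protected whatever the correlation, the inclusion number itself needs an allowance for loss.
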